##### Secondary endpoints

Additional sensitivity analysis will be performed by a per-protocol analysis for the primary endpoint. The risk difference of postoperative hearing deterioration will be supplemented by a 95% Wald confidence interval, and the Mantel-Haenszel estimation (with tumor size according to Koos as strata variable) will be performed as a sensitivity analysis as well as an additional per-protocol analysis. The secondary outcome postoperative deterioration of cochlear nerve function of at least one grade according to the GR compared with its preoperative function will be analyzed similar to the primary outcome and results will be given as odds ratios including 95% Wald confidence intervals and p-values. Deterioration of BAEPs amplitudes and latencies of the intraoperative BAEP will be evaluated by comparing their differences between beginning and end of surgery using linear regression with covariates treatment group and tumor size (Koos I/II or Koos III/IV). Change in quality of life (SF-12, PANQOL, HHIE) will be also evaluated using linear regression with covariates treatment group and tumor size (Koos I/II or Koos III/IV). All analyses of secondary endpoints will be interpreted in an exploratory sense.

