#### Secondary outcomes

The secondary endpoints are the following:
Late postoperative cochlear nerve function measured at follow-up 3 to 6 months after surgery according to GR 1–3 versus GR 4–5 (binary)Postoperative deterioration of cochlear nerve function of at least one grade according to the GR compared with its preoperative function (binary)Late postoperative deterioration of cochlear nerve function of at least one grade according to the GR compared with its preoperative function measured at follow-up 3 to 6 months after surgery (binary)Change of pure-tone thresholds (PTA) and speech discrimination score (Word Recognition Score, WRSmax)GR and American Academy of Otolaryngology-Head and Neck Surgery (AAOHNS) scoresIntraoperative deterioration of brainstem audiometry evoked potential (BAEP) mean values (amplitudes and latencies)Subjective quality of life/psychosocial impairment will be assessed by the means of three patient’s questionnaires (Hearing Handicap Inventory for the Elderly (HHIE), Short Form (SF)-12, Penn Acoustic Neuroma Quality of Life (PANQOL)) before surgery and at follow-upAnatomical preservation of the cochlear nerve and preservation of wave V (BAEP)Safety data

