### Sample size

The sample size calculation is based on the combined results of the pilot study and the multi-center study regarding the primary outcome postoperative cochlear nerve function [9, 15, 16]. Considering patients with tumor size Koos I–IV and preoperative hearing function GR 1–3, 30 out of 46 patients (65.2%) suffered from deaf in the control group versus 31 out of 63 patients (49.2%) in the therapy group. Using these frequencies, based on a two-sided chi-square test with alpha = 5% and 80% power and an interim analysis at information fraction 0.5 with O’Brien-Fleming-type alpha-spending and possible trial stop because of futility, requires 80 patients per group in the first stage. Additional 79 patients per group are necessary if the trial is not stopped because of futility after the interim analysis (SAS® procedure SEQDESIGN). Assuming a dropout rate of 5%, the planned sample size for the trial is 84 patients per treatment group in the first stage and 84 additional patients per group in the second stage. Finally, the total maximum number of patients required for both stages is 336 (168 before interim analysis and 168 after interim analysis).

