#### Audiometry/GR evaluation

Standard pure-tone audiometry provides diagnostic information concerning the degree, type, and configuration of hearing loss. Audiometries should be performed in a soundproof booth. Parameters are defined in International Organization for Standardization (ISO) norm (ISO 11957:1996, 1996). Speech audiometry is performed to obtain the speech recognition threshold by using German multisyllabic words (“Freiburger Zahlentest”), if possible, and suprathreshold speech recognition by using German monosyllabic words (“Freiburger Einsilbertest”), if possible. The following information should be provided additionally regarding the performed pure-tone and speech audiometries for both ears in each patient:
Pure-tone thresholds for air conduction at frequencies of 0.25, 0.5, 1, 2, 3, 4, and 8 kHz. Masking has to be applied if needed.Pure-tone thresholds for bone conduction at frequencies of 0.5, 1, 2, 3, 4, and 6 kHz. Masking has to be applied if needed.The graph plotted by connecting all hearing threshold values for all tested frequencies as well as masking levels used.Speech reception threshold (SRT) for air conduction (ipsilateral headphone-presentation, “Freiburger Zahlentest”).If SRT < 65 dB sound pressure level (SPL): word recognition score for Freiburger Monosyllables at 65, 80, and 95 dB SPL, using 2 lists each, masking levels have to be reported.If SRT ≥ 65 dB SPL and SRT < 80 dB SPL: word recognition score for Freiburger Monosyllables at 80 and 95 dB SPL, using 2 lists each, masking levels have to be reported.If SRT ≥ 80 dB SPL: word recognition score for Freiburger Monosyllables at 95 dB SPL, using 2 lists, masking levels have to be reported.

GR evaluation: Hearing class is determined according to the GR grading system [17] by the investigator of each trial site for inclusion. If speech discrimination (WRS_max_) is not available, evaluation will be done by pure-tone measurements only. For statistical analysis, it is additionally evaluated by an independent expert. AAOHNS evaluation will only be done by a blinded expert [19].

If during surgery the nervus cochlearis has been cut, grading is considered as GR 5. In this case, postoperative audiometries do not have to be performed.

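### The BAEP latency regression can use only ears whose wave survives surgery, so it compares arms on subsets selected by an outcome the drug is meant to affect

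*Protocol article*

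**What the plan says.** Four places in the protocol article bear on this.

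- **Final analysis, Secondary endpoints.** Deterioration of BAEP amplitudes and latencies "will be evaluated by comparing their differences between beginning and end of surgery using linear regression with covariates treatment group and tumor size". The section gives no value or rank for a wave that is absent at the end of surgery. It also declares all secondary analyses exploratory.
- **Methods for additional analyses.** BAEP status is a planned subgroup variable with three levels: stable, worsened and totally lost. Complete loss is therefore an expected result.
- **Audiometry/GR evaluation.** A cochlear nerve cut during surgery is graded GR 5. On the audiogram the section adds: "In this case, postoperative audiometries do not have to be performed".
- **Secondary outcomes.** The list includes "Change of pure-tone thresholds (PTA) and speech discrimination score". The analysis section names no model for it. Preservation of wave V is a separate endpoint in the same list.

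**The concern.** A latency difference needs a latency at both ends of the operation. An ear that has lost its wave cannot supply the second one, so the regression as written runs on ears with a surviving wave. Survival of the wave occurs after randomization, and nimodipine is given to improve it. Conditioning on it gives up the protection of randomization, and adjusting for Koos stratum does not restore it.

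The direction of the bias is unfavourable. If the drug saves borderline ears, these are likely to have long latencies. They enter the nimodipine mean, while their counterparts in the control arm are lost and enter no mean. A protective drug can then look weaker than it is on latency, or even harmful.

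A similar gap exists for PTA and WRSmax after a cut nerve. The authors assigned a worst value on the GR scale but none on the continuous scales. Because no model is stated for that endpoint, this is a secondary point.

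**Working it through.** **The plan's own figure.** The article gives no figure for lost waves, cut nerves or latency variability. Its one planning calculation is the sample size. With 30/46 and 31/63, two-sided 5% and 80% power, a fixed design needs 149 per arm. Multiplying by 1.056 (one look at information fraction 0.5, O'Brien-Fleming-type spending, non-binding futility) gives 157.3, or 151.36 × 1.056 = 159.8 with the log-odds-ratio variance. The plan has 80 + 79 = 159, so the figure reproduces. It does not depend on the present point.

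**Inputs for the check.** All loss rates and all dB and SD values below are assumptions. Let l0 and l1 be the proportions of ears without a measurable value under control and nimodipine. Let k0 = 1 - l0, k1 = 1 - l1, and r = k1 - k0 (ears saved only by nimodipine). Differences are nimodipine minus control, and positive means nimodipine looks worse.

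**Model A: common threshold, pure shift.** Damage is normal with SD 1, ears above a fixed threshold are lost, and nimodipine shifts all damage down. With z0 and z1 the normal quantiles of k0 and k1, the true shift is -(z1 - z0). The measured-only difference is -(z1 - z0) - φ(z1)/k1 + φ(z0)/k0.

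For 25% against 16%: z0 = 0.674 and z1 = 0.994, so the shift is -0.320. The measured-only difference is -0.320 - 0.290 + 0.424 = -0.186.

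| Assumed loss, control / nimodipine | True shift (SD) | Measured-only (SD) |
|---|---|---|
| 40% / 28% | -0.33 | -0.15 |
| 25% / 16% | -0.32 | -0.19 |
| 10% / 6% | -0.27 | -0.21 |

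The sign is kept; the effect shrinks.

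**Model B: three kinds of ear.** Some ears are kept in either arm, some are saved by nimodipine, and some are lost in either arm. Suppose saved ears measure d worse than control ears kept in either arm, and nimodipine improves the latter by b. Then

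measured-only difference = (r·d - k0·b) / k1.

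This holds in any unit, so it applies to latency as well as to dB. The sign is wrong when r·d > k0·b, that is, when d exceeds b × k0/r:

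- 40% / 28%: 0.60/0.12 = 5, so d > 5b
- 25% / 16%: 0.75/0.09 = 8.3, so d > 8.3b
- 10% / 6%: 0.90/0.04 = 22.5, so d > 22.5b

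With b = 0 any d > 0 gives the wrong sign. With a real benefit in kept ears, reversal needs saved ears to be much worse, and increasingly so as losses become rarer.

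**Model B on a dB scale** (for the PTA point). Kept ears worsen by 15 dB, saved ears by 30 dB, lost ears are assigned 60 dB, and b = 0. For 25% / 16%:

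- measured-only: (0.75 × 15 + 0.09 × 30)/0.84 - 15 = 16.6 - 15 = +1.6 dB
- all ears: (11.25 + 2.7 + 0.16 × 60) - (11.25 + 0.25 × 60) = 23.55 - 26.25 = -2.7 dB

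| Assumed loss | Measured-only (dB) | All ears (dB) |
|---|---|---|
| 40% / 28% | +2.5 | -3.6 |
| 25% / 16% | +1.6 | -2.7 |
| 10% / 6% | +0.6 | -1.2 |

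Simulated regressions on treatment and stratum (159 per arm, SD 15 dB, 800 runs) show what one trial would see. At 25% / 16% the measured-only estimate averaged +1.7 dB, had the wrong sign in 83% of runs and was significantly wrong in 12%. At 10% / 6% it averaged +0.7 dB, with 64% and 6%.

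With b = 5 dB at 25% / 16% and saved ears at 30 dB, the measured-only difference is (0.09 × 15 - 0.75 × 5)/0.84 = -2.9 dB, against -6.5 dB with all ears. The effect is diluted, not reversed.

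**The case against.** The strongest reply is that little depends on this. A cut nerve counts as GR 5, so the primary endpoint and the GR-based secondary endpoints keep those ears. Preservation of wave V is its own endpoint, so BAEP loss would be reported beside any latency result. The analyses concerned are exploratory. All of this stands and lowers the weight of the point. It does not remove the selection: exploratory status limits what may be claimed from an estimate but does not make it unbiased.

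A second reply is that an article condenses the full protocol, which may hold a rule for absent waves. That is fair for missing detail. Here, however, the article names a method, and that method cannot take an outcome the article itself expects.

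Several stronger readings are tempting, and the document does not support them.

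- A reader might infer that PTA and WRSmax changes are also regressed on measured values only. The regression sentence covers BAEP alone, and the exclusion of missing outcomes is written for the primary endpoint.
- A reader might infer that all deaf ears go unmeasured. Audiometry is waived, not barred, and only after a cut nerve.
- A reader might take the planning data, "30 out of 46 patients (65.2%) suffered from deaf in the control group versus 31 out of 63 patients (49.2%) in the therapy group", as the rate of missing values. These are hearing-grade outcomes. A GR 4 ear can have measurable thresholds, and a deaf ear with an intact nerve still gets its audiogram.
- A reader might extend the point to amplitude with equal force. A lost wave can be given amplitude 0; only latency has no natural value.

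**Conclusion.** The point holds for BAEP latency. The stated regression can compare only ears with a surviving wave, and wave survival is something the treatment is meant to change. For PTA and WRSmax it holds in a weaker form: the article assigns GR 5 to a cut nerve but no value on the continuous scales, and states no model.

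The size cannot be fixed from the document. Under a pure shift with assumed losses between 40%/28% and 10%/6%, the measured-only analysis shows between just under half and three quarters of the true effect (0.153/0.329 to 0.205/0.273). Reversal is possible when saved ears measure poorly and the drug does little for ears that would be kept anyway. A reader should not infer that nimodipine will look harmful: with a modest benefit in kept ears, the same loss rates only dilute the effect.

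This is a real but contained flaw in exploratory endpoints. It does not touch the primary analysis, the GR-based endpoints or the sample size.

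**What to change.** State the following before the data are analysed.

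1. **BAEP latency.** Analyse it as an ordered outcome using the article's own three levels, from stable through worsened to totally lost, by proportional-odds regression on treatment and tumor size. Alternatively, use a rank test stratified by tumor size with lost waves ranked worst. Define the boundary between stable and worsened in advance. Say how ears with no wave at the start of surgery are handled, the same way in both arms, and report their number.
2. **BAEP amplitude.** Set the end-of-surgery amplitude to 0 for a lost wave, so that every ear with a starting value stays in the regression.
3. **PTA and WRSmax.** Give ears with a cut nerve a pre-specified worst value (for example PTA at the audiometer limit and WRSmax 0%) or the worst rank.
4. **Measured-only means.** Report them as descriptive, with the number of ears without a value in each arm.

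The change is to analysis wording; conduct and sample size stay as they are. The price is an odds ratio or rank effect for latency, which is less familiar than a mean difference, and for PTA some dependence on the worst value chosen, which a rank analysis avoids.

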#### Questionnaires

Patients are asked for an evaluation of subjective health and communication competencies (quality of life) via three different patient questionnaires (SF-12 [20, 21], PANQOL [22], HHIE [23, 24]) twice during the trial: before surgery and during follow-up after 3 to 6 months. Interpretation of questionnaires and calculation of scores is highly standardized but will nevertheless be done by a blinded expert.

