##### Methods for additional analyses, such as subgroup analyses and adjusted analyses

Additionally, logistic regression analyses of the primary endpoint adjusted for tumor size (Koos classification and volumetry), preoperative hearing, extent of resection, positioning of the patient during surgery (semi-sitting or supine), total dose of nimodipine, dose modification (yes/no), and intraoperative events, e.g., bleedings (yes/no), as well as subgroup analyses by the following subgroups are planned:
Preservation of cochlear nerve intraoperative by surgeons’ statement (yes/no)Cystic tumor by blinded expert evaluation (yes/no)SexBAEP (amplitude and latency: stable/worsened/totally lost)

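### The quality-of-life regressions leave out the preoperative score, although it is collected: the comparison stays unbiased but loses precision and leaves chance baseline imbalance uncorrected

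*Protocol article*

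**What the plan says.** Under Final analysis, Secondary endpoints, the protocol article names the outcome as "Change in quality of life (SF-12, PANQOL, HHIE" and says that it "will be also evaluated using linear regression with covariates treatment group and tumor size (Koos I/II or Koos III/IV". The covariate list is therefore explicit and has two entries: treatment and the randomisation stratum.

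The Questionnaires section says that patients complete the three instruments "twice during the trial: before surgery and during follow-up after 3 to 6 months". A preoperative score should therefore exist for each patient.

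The section on additional analyses does use a baseline value, but only in "logistic regression analyses of the primary endpoint adjusted for tumor size (Koos classification and volumetry), preoperative hearing, extent of resection" and further factors. Nothing there reaches the quality-of-life models. The Secondary endpoints section closes with "All analyses of secondary endpoints will be interpreted in an exploratory sense".

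**The concern.** Subtracting the baseline is not the same as adjusting for it. A change score fixes the slope of follow-up on baseline at 1. When the true slope is smaller, change remains negatively correlated with baseline. Two things follow. The residual variance is larger than it needs to be, and an arm that starts higher by chance will show a smaller rise for that reason alone. Tumour size in the model removes only the part of the baseline score that the Koos stratum explains.

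At stake is how sharply the trial can speak on patient-reported outcome. The Objectives and Discussion sections expect preserved hearing to improve quality of life, and the questionnaires are the only direct measurement of that. The sample size was set for the binary hearing endpoint, so nothing else in the plan protects precision here.

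**Working it through.** **1. The plan's own figure.** The article gives no standard deviation, correlation, effect size or power for quality of life. Its only design figure is for the primary endpoint, from "30 out of 46 patients (65.2%) suffered from deaf in the control group" and "31 out of 63 patients (49.2%) in the therapy group". With pooled variance, a two-sided 5% level and 80% power, a fixed design needs about 149.9 per group. Assuming O'Brien-Fleming-type alpha and beta spending at half the information and a non-binding futility bound, the inflation factor is 1.056. This gives 149.9 × 1.056 = 158.3, rounded up to 159, which matches the stated 80 + 79. With 5% dropout, 159 / 0.95 = 167.4, so 168 per group and 336 in total. The figure reproduces, and no quality-of-life quantity enters it.

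**2. Variance of the two models.** Let the baseline have SD 1 and let b be the slope of follow-up on baseline within arm and stratum. Then

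residual variance of change = residual variance with baseline + (1 - b)².

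The second term cannot be negative, so in large samples the adjusted model is never less precise. The two are equal only when b = 1. With equal SDs before and after, b = rho, and

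- change without baseline: (1 - rho²) + (1 - rho)² = 2(1 - rho)
- with baseline: 1 - rho²
- ratio, adjusted to unadjusted: (1 + rho)/2

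**3. Numbers.** Here rho is an assumption shown over a range. Power is for an effect that the planned model would detect with 80% power, at 159 per arm.

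| rho | Change model | With baseline | Variance cut | Power with baseline | Shift per 1 SD imbalance |
|---|---|---|---|---|---|
| 0.4 | 1.20 | 0.84 | 30% | 91.8% | -0.6 SD |
| 0.5 | 1.00 | 0.75 | 25% | 89.9% | -0.5 SD |
| 0.6 | 0.80 | 0.64 | 20% | 87.9% | -0.4 SD |
| 0.7 | 0.60 | 0.51 | 15% | 86.0% | -0.3 SD |
| 0.8 | 0.40 | 0.36 | 10% | 84.0% | -0.2 SD |
| 0.9 | 0.20 | 0.19 | 5% | 82.0% | -0.1 SD |

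The variance cut does not depend on the number of patients. The power column would change little if fewer than 159 per arm returned both questionnaires, because it is anchored at 80% for the planned model.

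**4. Chance imbalance.** With 159 per arm the baseline difference between arms has standard deviation √(2/159) = 0.112 SD. A simulation of 8,000 trials at rho = 0.5, with a binary tumour-size covariate in both models, gave:

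- Mean treatment estimate under no effect: -0.001 SD for the planned model and 0.000 SD for the adjusted one. Both are unbiased over randomisation.
- Variance ratio, planned to adjusted: 1.31, against a theoretical 1/0.75 = 1.33.
- In the 9% of trials where the treated arm started more than 0.15 SD higher (mean 0.20 SD), the planned estimate was off by -0.10 SD on average, as -(1 - 0.5) × 0.20 predicts. The adjusted estimate was off by 0.00.

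**The case against.** The planned analysis is valid. A change-score regression that includes the stratification factor is a legitimate estimator in a randomised trial. The article contradicts nothing here, and it labels these endpoints exploratory. No confirmatory claim rests on them: the stated aim is hearing preservation, and better quality of life is presented as its consequence. All of this stands, and it keeps the point small.

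The size of the gain is also not known. It depends on a correlation that the article does not give, and at 0.8 to 0.9 it is only 10% to 5%. It further assumes equal variances before and after surgery. This stands as a limit on the magnitude but not on the direction, since step 2 holds for any slope.

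Finally, a journal article condenses the full protocol, and a statistical analysis plan may add the baseline. This carries less weight. The article does not leave the model open; it names the covariates. If a fuller document already includes the baseline score, the two should be brought into line.

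**Conclusion.** The point holds for SF-12, PANQOL and HHIE, as a worthwhile and nearly free improvement to three exploratory models. Under equal pre/post variances and an assumed correlation of 0.4 to 0.9, baseline adjustment lowers the variance of the treatment estimate by about 30% to 5% and removes a conditional shift of -(1 - rho) times any chance baseline difference.

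A reader might infer three stronger things that the documents do not support.

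- *That regression to the mean biases the comparison.* Under randomisation it acts equally in both arms on average. There is no systematic bias and no inflation of type I error; only the shift tied to a chance imbalance in a given trial remains.
- *That patients could be saved.* The 336 come solely from the binary hearing endpoint. The variance cut buys precision on quality of life and does not make the trial smaller.
- *That the BAEP models have the same defect and the same remedy.* They are also specified by "comparing their differences between beginning and end of surgery using linear regression with covariates treatment group and tumor size". However, the Interventional group section starts nimodipine on the day before surgery. The value at the beginning of surgery is therefore recorded after treatment has begun in one arm only. Conditioning on it could remove part of a treatment effect or bias the comparison, and the properties shown above do not carry over.

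**What to change.** Add the questionnaire's own preoperative score to each of the three quality-of-life regressions: follow-up score (or change) on treatment group, Koos stratum and baseline score. Once baseline is in the model, either form of the outcome gives the same treatment estimate, so results can still be reported as change.

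State that the baseline questionnaire must be completed before study treatment starts. The article's text says only that it precedes surgery, and the infusion begins the day before; the visit schedule figure, which may settle this, was not available for this review.

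Leave the BAEP models without the beginning-of-surgery value as an adjuster.

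The cost is one covariate per model and one residual degree of freedom, with no new data collection. The change should be fixed before the outcome data are analysed. The primary analysis, the interim analysis and the sample size stay as they are.
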